#### (13) rTMS treatment

For a duration of 4 weeks, the investigational medical device will be applied by the medical staff once a day for 20 minutes each session. Additionally, the medical staff responsible for administering the stimulation will create a log after each session. The subject log will include the application date, application status, start time of application, and any adverse reactions if they occur.

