#### **D. Masking**

In this clinical trial, "blinding of evaluators" will be maintained.

① Participants: The stimulation coil with 8-shaped design is capable of mode changes. In the sham mode, a sound similar to the sound of the magnetic field being generated will occur, but no actual magnetic field will be generated. In the active mode, a real magnetic field will be generated, providing rTMS stimulation. The appearance of the device, sound, and the time of applying the rTMS coil are the same. Participants who are receiving rTMS stimulation for the first time may find it difficult to discern whether they are receiving active or sham stimulation. However, participants who have experienced the trial device at least once before may feel sensations or discomfort when receiving active stimulation, making complete blinding challenging.

② Operator: The individual delivering the rTMS stimulation will select either the sham or active mode from the coil, making them unblinded.

③ Investigator (Principal Investigator): The investigator enrolls patients who meet the criteria and are willing to participate in the study, as well as verifies patient conditions during outpatient visits. However, they will remain blind to which group the patients are assigned to.

④ Evaluator: Three independent assessors will evaluate cognitive function. These assessors will be blinded to which group the patients are assigned to.

⑤ Emergency Unblinding Procedure: In case of severe medical emergencies on a case-by-case basis, unblinding by the investigator might be considered. If the trial responsible person deems unblinding necessary, it will be performed. In such cases, the trial responsible person will ensure records of the unblinding procedure are maintained.

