#### **E. Stimulation Protocol**

-Stimulation Frequency: 20 Hz, delivering stimulation at 20 Hz for 2 seconds in each train, followed by a 28-second rest period. A single stimulation site will receive a total of 40 trains (a total of 1600 pulses) in one session.

Stimulation Intensity: 100% of the motor threshold (MT), which can be decreased to 70% of the motor threshold in case of pain. Motor threshold is determined by stimulating the contralateral

motor cortex with TMS for 10 trials while the target muscle (Abductor pollicis brevis) is at rest. The lowest intensity that elicits visible muscle contractions in the target muscle for 5 out of 10 trials is selected as the motor threshold. This measurement will remain constant throughout the 4-week stimulation period.

-Stimulation Site: The stimulation site will be determined based on the resting functional MRI analysis of the baseline scan. The left lateral parietal region with the highest connectivity to the hippocampus will be selected for stimulation. During the 4-week stimulation period, an individualized medical guide will be used to fix the TMS transducer on the patient's scalp for accurate and consistent targeting. This medical guide will be produced using 3D printing based on the patient's brain MRI information, ensuring a customized fit for each patient.

-Duration: More than 20 minutes per session. Stimulation Period: Stimulation will be administered 5 times per week (Monday to Friday) for a total of 20 sessions over a 4-week period.

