10) The acquisition of Diffusion Tensor Image and resting fMRI will be carried out simultaneously with MRI imaging (i.e., during the MRI scan). This means that any side effects associated with MRI will also apply to the acquisition of diffusion tensor image and resting fMRI. A portion of the 30-minute MRI scan will be dedicated to acquiring the diffusion tensor image and resting fMRI data. The information obtained from the fMRI will be used to create a customized 3D-printed guide for accurately positioning the TMS transducer on the patient's head for targeted treatment. This guide will ensure precise guidance for the treatment location based on the patient's individual data.

11) Any newly occurring symptoms or signs after rTMS application, as well as any worsening of underlying conditions, will be documented.

12) The presence of any adverse events will be assessed after each of the 20 sessions of rTMS stimulation.

13) If an EEG (electroencephalogram) test has been conducted within the past 6 months before the enrollment date, the results of that test can be collected and utilized as a replacement for the current study's EEG assessment.

14) If an ECG (electrocardiogram) test has been conducted within the past 6 months before the enrollment date, the results of that test can be collected and utilized as a replacement for the current study's ECG assessment.

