### 14.2 Method for Safety Evaluation

The safety is evaluated through adverse events and vital signs. All reported adverse events following rTMS application will be summarized in terms of severity and causality. The frequency and percentage of the number of participants and occurrences of adverse events will be presented in a chart. As for vital signs, continuous variables will be summarized using mean, standard deviation,

median, and range, while categorical variables will be summarized using frequency and percentage. Additionally, clinically significant results will be summarized and presented separately.

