#### **(2) Causality**

The clinical trial personnel should determine the causality according to the assessment criteria and indicate it on the adverse reaction record form.

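### Adverse reactions at the 20 sessions are first logged by unblinded staff, and section 14.3.2 does not reserve severity and causality ratings to the blinded investigator

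*Protocol*

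**What the plan says.** **Who logs at the session.** Protocol section 10.A(13) states that "the medical staff responsible for administering the stimulation will create a log after each session". On content it adds: "The subject log will include the application date, application status, start time of application, and any adverse reactions if they occur".

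**Who is blind.** Section 9.D says of the operator: "The individual delivering the rTMS stimulation will select either the sham or active mode from the coil, making them unblinded". Of the investigator it says: "However, they will remain blind to which group the patients are assigned to". The three cognitive assessors are also blind.

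**When events are checked.** Footnote 12 to the section 10 schedule reads: "The presence of any adverse events will be assessed after each of the 20 sessions of rTMS stimulation". It names no assessor.

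**Who assesses and rates.** Section 10.A(14) has the investigator interview participants and assess whether events occurred and what they were, in a record that covers severity and causality. The last paragraph of section 11.3 has the investigator enter anticipated side effects and their severity level in the case report form. Section 14.3.2(2) says instead: "The clinical trial personnel should determine the causality according to the assessment criteria and indicate it on the adverse reaction record form". Section 14.3.2(1) gives severity to the same undefined group, and 14.3.2(5) adds the clinical coordinator's opinion.

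**How the results are used.** Section 14.2: "All reported adverse events following rTMS application will be summarized in terms of severity and causality".

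**The concern.** The side effects that the section 14.1 table lists as frequent (headache, localized pain, neck pain, paresthesia) are subjective and leave no trace unless someone asks about them and writes the answer down. At the sessions, the one person the protocol names as writing something down has just chosen sham or active mode. Someone who knows that no field was generated may be slower to note a headache, or to call it device-related, than someone who knows that one was.

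Severity and causality are the judgements most open to such knowledge, and they are the two dimensions of the section 14.2 summary. Section 7.D presents the trial as groundwork for a confirmatory study. If arm knowledge shapes the harm record, any reading of active against sham would mix a device effect with a recording effect.

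**Working it through.** This is mainly a comparison of provisions. The only figures are counts.

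**Step 1: the session count.** Section 9.E: "Stimulation will be administered 5 times per week (Monday to Friday) for a total of 20 sessions over a 4-week period". 5 × 4 = 20. The section 10 schedule puts the sessions at Visits 4 to 23, and 23 − 4 + 1 = 20. The figure reproduces.

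**Step 2: how many session logs.** With 16 participants per arm (section 7.D) and full attendance, 20 × 16 = 320 per arm and 2 × 320 = 640 in all. This assumes that the schedule, headed as being for the rTMS group, also governs the sham group. Its device-application row names both groups.

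**Step 3: share of scheduled checks that fall at sessions.** After randomisation, adverse events are checked at 20 sessions, at Visits 24-25 (one or two contacts) and at Visit 26 (one contact).
- One contact at Visits 24-25: 20 / (20 + 1 + 1) = 20/22 = 90.9%.
- Two contacts: 20 / (20 + 2 + 1) = 20/23 = 87.0%.

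This shows where the checks fall. It does not show that the operator is the only person who asks.

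**Step 4: provisions side by side.**

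| Task | Protocol section | Who | Blind to arm? |
|---|---|---|---|
| Session log, including adverse reactions | 10.A(13) | Staff delivering stimulation | No (9.D) |
| Check after each session | 10 schedule, footnote 12 | Not named | Not stated |
| Interview; occurrence and details of events; record includes severity and causality | 10.A(14) | Investigator | Yes, if the investigator of 9.D |
| Name and severity of anticipated side effects | 11.3, last paragraph | Investigator | Yes, on the same reading |
| Severity on the reaction form | 14.3.2(1) | Trial personnel, undefined | Not stated |
| Causality on the reaction form | 14.3.2(2) | Trial personnel, undefined | Not stated |
| Opinion on the reaction | 14.3.2(5) | Clinical coordinator | Not stated |

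**Step 5: what follows.** Two places point to a blinded assessor. Section 14.3.2 uses a wider term that does not exclude the operator. No provision says that severity or causality must be rated without knowledge of the arm. Unblinded rating is thus allowed without being prescribed.

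**Step 6: what is captured.** Section 10.A(14) and footnote 11 cover any new symptom or sign and any worsening of an underlying condition, whatever the cause. The session log speaks of adverse reactions, so its writer may attribute before recording. The wider route relies on voluntary reports, interviews and unspecified questionnaires. Participants qualify through delayed recall at least 2 standard deviations below the mean (section 7.B, criterion 3). A later interview may therefore miss a transient symptom that was not written down on the day.

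**The case against.** The case on the other side is substantial.

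- **The protocol already uses a blinded assessor for harms.** A reader might infer that the trial's blinding is not applied to safety at all. Sections 10.A(14) and 11.3 contradict that, because both name the investigator, whom 9.D keeps blind. This stands.
- **Section 14.3.2 does not name the operator.** A reader might infer that causality in the rTMS arm would be rated by someone who knows that a real field was applied. The text does not say so. The term is undefined in what reads as a translation and can be read consistently with 10.A(14). This stands as far as it goes: the wording permits unblinded rating and does not require it.
- **Section 10.A(13) is a treatment log.** It assigns neither severity nor causality, and an event missing from it can still reach the adverse event record by another route. This stands, but it does not remove the dependence on the session record for short-lived symptoms.
- **No between-arm safety comparison is clearly planned.** The group comparisons in section 6.A concern cognition and imaging, section 14.2 is descriptive, and the opening of section 14 frames the safety set around rTMS application, although 14.3.1 covers all participants. This limits the consequence without removing it, since severity and causality are summarised in any case.
- **The operator's unblinding is declared openly.** This is agreed. No blinding promise is broken.

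**Conclusion.** The point holds in a limited form. Staff who know the arm log adverse reactions at each of 20 sessions, the footnote requiring a check at each session names no assessor, and section 14.3.2 leaves severity and causality open to personnel who may be unblinded, whereas sections 10.A(14) and 11.3 point to the blinded investigator.

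It would be tempting to put a percentage-point gap between arms on this. The documents give no event rates for this population and nothing on how completely each arm would be recorded, so any such figure would be pure assumption. What can be stated is exposure: 20 sessions per participant, up to 640 session logs, and 87% to 91% of scheduled post-randomisation checks falling at sessions. The effect matters most if the arms are compared.

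The conclusion assumes that the investigator in sections 10.A(14) and 11.3 is the one described as blind in 9.D, and that the schedule applies to both arms. It is a worthwhile, inexpensive improvement and does not show that the safety results would be biased.

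**What to change.** 1. Amend 10.A(13)-(14) so that after every session, in both arms, the participant (with a caregiver where present) answers the same fixed symptom questions based on the section 14.1 table. Every positive answer goes on the adverse event form, whatever the suspected cause.
2. Amend 14.3.2(1)-(2) to agree with 10.A(14) and 11.3: severity and causality are rated only by the investigator who is blind under 9.D, and not by the operator.
3. Keep the record of sham or active mode separate from the adverse event form. Actions taken with the device stay on that form, because 10.A(14) and 14.3.2(3) require them there.

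**Cost.** A short question sheet, a few minutes per session, and more minor events recorded in both arms. No extra staff are needed, since the investigator already assesses adverse events under 10.A(14). No treatment rule changes. One limit remains: the operator may still be present when the questions are asked, but fixed questions leave little to that person's discretion.

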#### (14) verification of adverse effect

To gather information about any adverse events, subjects will be encouraged to report voluntarily, and the investigator will regularly interview them during scheduled or additional visits. Through interviews, questionnaires, and medical assessments, the investigator will assess the occurrence and details of any adverse events. Adverse events will be documented if there are new symptoms/signs that emerge after the application of the investigational medical device or if there is a worsening of underlying conditions. The adverse event record will include the onset and resolution dates, severity, extent, outcomes, actions taken related to the investigational medical device, causality assessment, treatment provided for the adverse event, determination of whether it qualifies as a serious adverse event or medical device adverse reaction, and relevant details. All of this information will be recorded in the case report form.

## **11. Predicted Side Effects and Precautions during use**

The potential side effects that could occur during this clinical trial include:

### **11.1 repetitive Transcranial Magnetic Stimulatio (rTMS)[14]**

#### **(1) seizure**

The prevalence of epileptic seizure among patients with epilepsys is approximately 1.4%, while it is less than 1% among healthy individuals. No adverse events have been reported within the range of stimulation indicated by the safety guidelines. Individuals with epilepsy or those with a history of epileptic discharges in pre-trial EEG assessments will be excluded from participation in the clinical trial.

#### **(2) Transient acute hypomania induction**

Although the possibility of occurrence is mentioned after stimulation of the left prefrontal area, there have been no reported cases in the specific left lateral parietal area targeted in this study.

#### **(3) headache, neck pain, parathesia**

It is an occasional side effect. If a patient complains of pain, the intensity will be lowered to 70% of the motor threshold. If the pain persists even at 70%, the stimulation will be stopped, and the participant will be excluded from the study.

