#### 2) Secondary Outcome Measure

- 1) Study Design: Single-arm design
- 2) Allocation: Random assignment
- 3) -Compare changes in K-GDS short form and S-IADL scores between baseline, 4 weeks after rTMS stimulation, and 8 weeks after.  
-Compare changes in K-MMSE, K-MoCA, CDR-SOB, ADAS-Cog, COWAT, Stroop, TMT, RVP, SWM, PRM scores between baseline and after 4 weeks of rTMS stimulation.  
-Compare FA values in DTI analysis at 4 weeks after rTMS stimulation.  
-Examine functional network changes in resting-state fMRI at 4 weeks after rTMS stimulation.
- 4) masking: Blinded assessment by evaluators

- 1) Study Design: Parallel design
- 2) Allocation: Random assignment
- 3) Intervention Group: rTMS application group  
Control Group: Sham group (sham coil emits sound only, no rTMS stimulation)
- 4) -Compare K-MMSE, K-MoCA, CDR, ADAS-Cog, COWAT, Stroop, TMT, RVP, SWM, PRM scores between intervention and control groups after 4 weeks.  
-Compare FA values in DTI analysis between intervention and control groups at 4 weeks after.  
-Examine functional network changes in resting-state fMRI between intervention and control groups at 4 weeks after.
- 5) masking: Blinded assessment by evaluators

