#### **12.1.2 Handling of Study Termination**

Interventions or treatments will be administered to discontinued participants as necessary, and their progress will continue to be observed.

All test results, the date of discontinuation, reasons for discontinuation, subsequent interventions, and progress after discontinuation will be documented in the case report form

In case the clinical trial is terminated, the Clinical Trial Investigator will notify the Institutional Review Board (IRB) in writing about the termination along with the reasons for termination.

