### **12.2 Criteria for Withdrawal and Handling of Withdrawal**

#### **12.2.1 Criteria of Withdrawal**

- 1) Patient's Request: Any patient who wishes to withdraw from the study can do so, but they will receive counseling from the medical staff about the need for long-term follow-up observation.
- 2) Serious, unexpected, or life-threatening adverse events requiring treatment discontinuation.
- 3) When the medical judgment of the healthcare provider indicates that further participation in the series of follow-up tests could be detrimental to the patient's health or well-being.
- 4) Failure to comply with the regulations outlined in the clinical trial protocol.

If a participant is suspected to have progressed to dementia during the course of the clinical trial and they do not refuse, their participation in the trial will continue. This does not constitute a criterion for exclusion from the trial. However, if acetylcholinesterase inhibitors or memantine are subsequently added for the participant's benefit, this information should be recorded in the concomitant medication section of the case report form.

Participants can voluntarily withdraw from the clinical trial at any time for any reason. Participants who express their intention to withdraw, fail to attend scheduled visits, or otherwise fail to comply with follow-up observations may be considered as having dropped out of the trial prematurely.

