### **12.2.2 Handling of Withdrawal**

- Participants who withdraw from the clinical trial due to simple mood changes will be excluded from the study population.
- If the discomfort is not due to simple mood changes but is caused by the trial itself, the underlying reason will be analyzed and attached to the case report.

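### Section 11.1(3) removes a participant from the study, not just from stimulation, when pain persists, which could cost 4- and 8-week ADAS-Cog data mainly in the rTMS arm

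*Protocol*

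**What the plan says.** Section 11.1(3) of the protocol deals with headache, neck pain and paresthesia. Pain first leads to a reduction to 70% of motor threshold. If that fails: "If the pain persists even at 70%, the stimulation will be stopped, and the participant will be excluded from the study".

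Three other places bear on what happens next:

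- Section 12.1.2, on discontinued participants: "Interventions or treatments will be administered to discontinued participants as necessary, and their progress will continue to be observed". It adds: "All test results, the date of discontinuation, reasons for discontinuation, subsequent interventions, and progress after discontinuation will be documented in the case report form".
- Section 12.2.1, criterion 3, allows withdrawal where medical judgement is that "further participation in the series of follow-up tests could be detrimental to the patient's health or well-being".
- Section 12.2.2: "Participants who withdraw from the clinical trial due to simple mood changes will be excluded from the study population". For the other case it says: "If the discomfort is not due to simple mood changes but is caused by the trial itself, the underlying reason will be analyzed", with the result attached to the case report.

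On the two arms, section 9.A.2 describes the comparator as "Control Group: Sham group (sham coil emits sound only, no rTMS stimulation", and section 9.D notes that "participants who have experienced the trial device at least once before may feel sensations or discomfort when receiving active stimulation".

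Section 13.1.A makes the 8-week change in ADAS-Cog, and the difference in change scores at that time, the primary outcome.

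**The concern.** The rule in 11.1(3) joins two decisions that should be separate. One is clinical: do not go on stimulating someone who is in pain at the reduced intensity. The other concerns data: whether that person is still assessed at 4 and 8 weeks. The first does not require the second. A participant who stopped after, say, eight sessions can still sit the ADAS-Cog, and the protocol has its own criterion, 12.2.1(3), for the rare case where testing itself would do harm.

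At stake is selective loss of the primary outcome. Only active stimulation produces a field, so the trigger is linked to treatment. Those removed would be the rTMS participants who tolerated it worst, with no matching removal from sham. Both the change within the rTMS group and the contrast with sham would then rest on the rTMS participants who tolerated treatment. The protocol says the trial is meant to inform later confirmatory studies (section 7.D), and those studies need to know how people fare who cannot complete the course.

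**Working it through.** **Reading the text.** The protocol states no figure on this point, so there is nothing to reproduce. The passages compare as follows.

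| Place | What happens to the participant | 4- and 8-week ADAS-Cog? |
|---|---|---|
| 11.1(3) | Stimulation stopped; excluded from the study | Not mentioned; exclusion implies no |
| 12.1.2 | Treated as needed; progress observed; test results recorded | Not named |
| 12.2.1(3) | Withdrawn if follow-up tests could be harmful | No, for that reason |
| 12.2.2 | Trial-caused discomfort: reason analysed and attached | Not mentioned |

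In 11.1(3) the first clause already ends treatment, so the second clause naturally adds something more. No passage says whether the scheduled assessments go ahead after a stop for pain.

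**Timing.** In the section 10 schedule, stimulation occupies visits 4 to 23, the 4-week assessment is at visits 24 and 25, and the 8-week assessment is at visit 26. A stop for pain during stimulation therefore comes before every post-baseline ADAS-Cog. A participant excluded at that point would have a baseline score and nothing after it.

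**Scale.** Inputs from the protocol: 16 rTMS and 16 sham participants (sections 7.D and 9.B). Inputs not in the protocol, so assumed: the rate p of persistent pain per rTMS participant, the number k lost, and the difference D (in SD of the change score) between those lost and those kept. The protocol calls these symptoms occasional in 11.1(3) and frequent in its side-effect table, but gives no rate for pain persisting at 70%.

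*Chance of at least one exclusion among 16*, 1 − (1 − p)^16, treating participants as independent, and expected number 16p:

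| p (assumed) | Chance of at least one | Expected number |
|---|---|---|
| 1% | 0.149 | 0.16 |
| 2% | 0.276 | 0.32 |
| 5% | 0.560 | 0.80 |
| 10% | 0.815 | 1.60 |

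*Precision.* The 95% half-width in SD units is t(0.975, n−1)/√n for the rTMS change. For the difference from 16 sham participants with equal SD it is t(0.975, n+14)·√(1/n + 1/16):

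| rTMS n at week 8 | rTMS change | rTMS minus sham |
|---|---|---|
| 16 | 0.533 | 0.722 |
| 15 | 0.554 (+3.9%) | 0.735 (+1.8%) |
| 14 | 0.577 (+8.4%) | 0.750 (+3.8%) |

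*Bias.* If k of 16 are lost and differ by D from those kept, the rTMS mean among those kept is off by (k/16)·D. With sham complete, the difference shifts by the same amount:

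| | D = 0.5 SD | D = 1.0 SD |
|---|---|---|
| k = 1 | 0.03 | 0.06 |
| k = 2 | 0.06 | 0.13 |

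The largest shift here, 0.125 SD before rounding, is about 23% of the full-data half-width for the rTMS change (0.125/0.533).

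**The case against.** The best defence is that the two sections work in sequence: 11.1(3) triggers discontinuation and 12.1.2 governs what follows, so observation continues and test results are recorded. The text appears to be a translation, and the word for exclusion may mean no more than taken off treatment. A reader might infer that 11.1(3) and 12.1.2 flatly contradict each other. They do not; they are in tension. But 12.1.2 does not settle the matter, because observing progress could mean safety follow-up alone and the ADAS-Cog visits are not named.

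A reader might also infer that scores already collected from these participants are dropped from the analysis. Nothing says so. Section 13.2 plans a linear mixed-effects model over time points, which can use whatever visits exist, and the handling of data after stopping may properly sit in an analysis plan that was not available here. That answers a concern about the analysis set. It does not answer this one, because no model or analysis plan can recover visits that were never held, and exclusion during stimulation would leave no post-baseline score.

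Two supports should not be pressed too far. The remark in 9.D concerns blinding and says discomfort may occur; it does not speak of pain persisting after dose reduction. Section 12.2.2 excludes those who withdraw for mood changes but does not say that they alone are excluded. The expected imbalance between arms rests chiefly on sham producing no field, and its size is not documented.

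It is also fair that the trial is exploratory, has no power calculation to erode, and may see no such case. This limits the weight of the point, but the remedy is correspondingly cheap.

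**Conclusion.** The point stands in a limited form. Section 11.1(3) fixes a rule that, followed as written, ends assessment when only stimulation needs to end, and 12.1.2 does not clearly rescue the 4- and 8-week ADAS-Cog. Any loss would fall mainly in the rTMS arm and would affect both parts of the primary outcome.

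The size is unknown and probably modest. Every figure above depends on assumed values of p, k and D; the precision figures also assume equal SD and complete sham data. Selective loss is a possibility created by the wording, not a certainty.

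A reader might want to add two nearby matters. Section 12.1.1 ties discontinuation after a deviation to a significant safety risk, whereas 12.2.1(4) lists non-compliance without that condition. But 12.1.1 also lets missed visits or failed follow-up count as termination, so the sections are closer than they first look, and no effect on results is shown. Two bullets in 12.1.1 speak of halting the trial where stopping one participant's stimulation is most likely meant. Both are minor editorial matters and not part of this finding.

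**What to change.** Reword the last sentence of 11.1(3) along these lines: *stimulation will be stopped; the participant remains in the study, and the 4- and 8-week assessments, including ADAS-Cog, are still sought unless consent is withdrawn or testing is judged harmful under 12.2.1(3)*. Add a cross-reference to 12.1.2.

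The trigger for stopping stimulation is unchanged, so participants lose no protection. The cost is one wording change and a few follow-up visits for those who stop early, in keeping with the continued observation that 12.1.2 already provides for.
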